## Abstract

**Purpose:**

Parents of children with autism spectrum disorder (ASD) often lack the knowledge and confidence to implement early intervention. This study will evaluate the effects of a parental self-efficacy promotion program on parenting self-efficacy, parenting stress, intervention compliance, and family quality of life for parents of children with ASD.

**Design and methods:**

This two-arm, pretest, post-test quasi-experimental study recruits 80 parents in one tertiary hospital in China. The control group receives routine care, and the intervention group receives a 1-month self-efficacy promotion program on the basis of usual care. This program consists of one face-to-face session and three online sessions, supplemented by a written pamphlet. Content includes goal setting, experience sharing, verbal encouragement, and mobilizing of positive emotions.

**Conclusion:**

This study will empower the nurses as leaders to promote the well-being of parents of children with ASD and improve the early family intervention for their child by providing a parental self-efficacy promotion program.

**Practice implications:**

Parents need support to implement intervention in the family for their child with ASD. A nurse-led program targeted at improving parental self-efficacy is worth considering.

## Introduction

Autism spectrum disorder (ASD) encompasses a set of neurodevelopmental conditions with core symptoms of social interaction difficulties and stereotypical behavior (1). The prevalence of ASD has been increasing globally, with 2.8% in the United States and approximately 0.7% in China (2, 3). Early and continuous intervention is crucial for language development, social interaction, cognition, and reduction of stereotyped behaviors in children with ASD (4, 5). A study found that around 20% of individuals with ASD did not receive any intervention after diagnosis (6). Additionally, a European study revealed that 61.61% of children with ASD received intervention within 2 months of diagnosis (7), however, in southern China, less than one-third of families received home-based intervention within 1 month after diagnosis (8, 9), highlighting the need to improve early and long-term intervention rates. Parents play a vital role as primary caregivers and their fidelity in implementing early intervention significantly impacts children’s outcomes (10). Unfortunately, parents of children with ASD generally lack knowledge in implementing ASD training and exhibit lower levels of parenting self-efficacy, especially during the early stage of diagnosis (11, 12), which is positively correlated with negative coping strategies and may potentially influence the child’s progress (13). The financial burden of ASD interventions including significant costs over the lifetime of an individual, poses a considerable challenge for families and may affect access to ASD-related services and support (9, 14). Therefore, improving parents’ confidence, involvement, and intervention skills is essential to ensure the quality of early family intervention for children with ASD.

Parental self-efficacy (PSE) refers to parents’ beliefs in their ability to influence their child’s development through their process, motivation, and cognitive abilities (15). PSE directly influences parental behavior motivation and is formed and influenced by mastery experiences, vicarious experiences, verbal persuasions, and physical and affective states (16). Parents of children with ASD often experience lower levels of parenting self-efficacy compared to parents of typically developing children due to the specific symptoms associated with ASD (11). PSE is a significant predictor of family intervention for parents of children with ASD (17). Higher PSE is associated with the use of promotive parenting strategies, while lower PSE is correlated with higher levels of children’s emotional/behavioral behaviors and caregiver distress (18, 19). Moreover, lower PSE can also lead to a decrease in family quality of life (20).

The family plays a crucial role in the intervention; however, implementation of long-term early intervention is poor in most families (9). Studies have shown that PSE is positively correlated with active parenting practices (21), and more support for families to enhance self-efficacy is expected. Several studies have reported the effects of health education for parents of children with ASD (22–24), although most previous health education programs focused primarily on delivering ASD-related intervention knowledge and skills rather than targeting parental psychological mechanisms (10, 25). Ginn et al. (23) provided interactive training to 30 parent-child dyads with ASD, teaching mothers techniques to engage in social and playful behaviors with their child. This study reported significant improvements in children’s disruptive behaviors and mothers’ stress after the intervention and follow-up. Zhou et al. (26) implemented a pilot study including four times daily ASD-related rehabilitation training and psychoeducation for families of children with ASD. The results showed an improvement in parenting self-efficacy, and a decrease in anxiety and depression for parents.

Emerging studies have demonstrated that health education based on self-efficacy theory has been effective in increasing parental self-efficacy and improving disease management outcomes for parents of children with chronic diseases (27–29). For example, Cheng et al. (27) designed a randomized controlled trial (RCT) based on the self-efficacy theory for parents in controlling child’s eczema, which showed significant improvement in the child’s eczema severity and parental self-efficacy. Similarly, another RCT was conducted for parents of children with asthma, the intervention groups had significantly higher parental self-efficacy and 1.4 times the child’s experience of an asthma crisis improved compared to the control group post-intervention (da Rocha Mendes et al., 2024). However, non-significant results were also observed, an online platform was developed to enhance parental self-efficacy and of parents with a child with type 1 diabetes, the self-empowerment was not significant change post-intervention (30).

In summary, most existing ASD parents program emphasize knowledge or skills delivery (10), but relatively few have been designed primarily to enhance parental psychological such as PSE, or to target Bandura’s four sources of self-efficacy in a structured way (3). Therefore, this intervention will address the gap by testing whether a theory-driven, nurse-delivered PSE intervention improves parental self-efficacy, parenting stress, family quality of life and symptom severity post intervention and at 6-month follow-up. The hypotheses are as follows:

Compared with the control group, the intervention group will be expected to demonstrate higher parental self-efficacy scores at post-intervention and at 6-month follow-up.Compared with the control group, the intervention group will show higher improvements in secondary outcomes at post-intervention and at 6-month follow-up, including lower parenting stress, higher treatment compliance, family quality of life, and reduced child symptom severity.

### Theoretical framework

The intervention is based on Bandura’s self-efficacy theory, which suggests that human behavior is influenced by self-efficacy expectations and outcome expectations. Self-efficacy was reflected in this study as parents’ expectation of themselves to implement family interventions as behaviors (31). There are four aspects of Bandura’s self-efficacy theory, namely mastery experiences, which comes from the individual’s personal experience and is the primary source of self-efficacy; vicarious experiences, where experienced people share their experiences; verbal persuasions, which refers to the use of persuasive language to encourage an individual and increase their self-efficacy; and physical and affective states, which are primarily physiological and emotional reactions to a task faced by individuals (31). The content includes helping parents set training goals, providing them with the necessary knowledge and skills (mastery experiences). Experienced parents will participate in group sessions to share their experiences with others, fostering a sense of learning from peers (vicarious experiences). We will employ verbal persuasion throughout the intervention to commend parents who demonstrate good compliance and support those facing challenges in identifying difficulties and exploring potential solutions. Additionally, we will address the physical and affective states of parents by providing strategies to help them manage emotional distress (16).

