The first session will take place in the hospital’s meeting room before participants are discharged. The nurse will introduce herself, describe the intervention process, invite parents to join the intervention group’s WeChat group and provide a pamphlet. A PowerPoint presentation on “understanding ASD” and “the importance of parents in early family intervention” will be delivered. Subsequently, the nurse and a rehabilitation therapist will collaborate with parents to set individualized goals and content for home training based on their child’s specific needs. Lastly, parents will be instructed to complete a training record sheet to document daily training activities and reflections. The remaining three online sessions will be conducted via Tencent meetings. The second session will focus on strategies for integrating intervention into daily life and family management. The third session will focus on emotion management in the care giving process of children with ASD. The nurse and rehabilitation therapist will discuss the child’s intervention process, address challenges faced by parents in implementing and adhering to the intervention, assess achievements, and provide support in problem-solving and enhancing confidence in the intervention. In the fourth session, the nurse and parents will review the initial goals set by parents, assess progress and challenges encountered in adhering to the intervention, and discuss new goals or encourage persistence in implementing efforts. Within the group, 1–2 parents who have a proactive attitude toward the intervention and are willing to share their caring experiences may be invited to do so. They will provide insights and tips based on their experiences to facilitate learning and discussion among parents. With parental consent, a video demonstrating the parents implementing intervention for a child with ASD may be shown to inspire learning and discussion among parents. These four aspects are incorporated into each component of the intervention, as shown in **Table 2**.

**Table 2 T2:** Parental self-efficacy promotion components, strategies, and techniques.

Components	Strategies	Content

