### Sample size

The sample size calculation was performed using the Power Analysis and Sample Size (PASS) software (NCSS, Kaysville, Utah). Parenting self-efficacy was chosen as the primary outcome for sample size calculation. According to a study using the C-PSOC to evaluate the effects of psychoeducational therapy on parenting self-efficacy in parents of children with ASD, the mean ± standard deviation (*SD*) of average total parenting self-efficacy was reported as 6.99 (0.76) (26). Considering a 15% dropout rate and α = 0.05 (two-sided), PASS indicated that a total of 80 participants (40 participants in each group) would be required to achieve 80% power.

$$n_{1\;}=\;n_{2}\;=\;2\times [\frac{{\left(t_{\alpha }\;+\;t_{\beta }\right)}^{2}\;\times \;s^{2}}{\delta^{2}}]$$

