### Statistical methods

IBM SPSS 26.0 (IBM Corp., NY, USA) will be used for data analysis. Descriptive statistics such as mean, median, standard deviation, interquartile range, frequency, and percentage will be used to describe the baseline characteristics of the participants. The independent *t*-tests and one-way ANOVA will be used to compare the homogeneity of the two groups at baseline. Outcome analyses will be conducted based on the intention-to-treat (ITT) principle. Missing data will be imputed based on the results of Little’s missing completely at random (MCAR) test. The generalized estimating equations (GEE) model will be used to analyze the group and time differences in outcome variables. Potential covariates such as sociodemographic or clinical characteristics with a *P<*0.01 in the baseline will be considered in the adjusted GEE model. Open-ended contents will be summarized descriptively with selected anonymized quotations. Statistical significance will be set at 0.05 (two-sided).

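### Peer-group delivery in the intervention arm alone may correlate parents' outcomes, and neither the sample size nor the stated GEE allows for this; if the correlation is positive, the standard error of the program effect is too small

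*Protocol article*

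**What the plan says.** The Theoretical framework section makes learning from peers one of the four sources of self-efficacy that the program targets: "Experienced parents will participate in group sessions to share their experiences with others, fostering a sense of learning from peers (vicarious experiences". The Intervention group section places this in the sessions: "Within the group, 1–2 parents who have a proactive attitude toward the intervention and are willing to share their caring experiences may be invited". Table 2 also has parents learning from and talking with each other. Goal setting, by contrast, is done for each family individually.

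The Control group section describes ward nursing instruction and nurse telephone calls, with no group session. Under Preparation phase both arms have a WeChat group. The control group's chat is described for contact and data collection; Table 2 also uses the intervention chat to help parents with their questions.

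The Sample size section prints a formula for two independent samples. It states "Considering a 15% dropout rate and α = 0.05 (two-sided", and concludes that "a total of 80 participants (40 participants in each group) would be required to achieve 80% power". No group size, ICC or design effect appears. On the analysis, Statistical methods says: "The generalized estimating equations (GEE) model will be used to analyze the group and time differences in outcome variables". The only adjustment listed is for baseline covariates, and no session group or intake cohort is mentioned. The size, number and composition of the session groups are not given anywhere in the article.

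**The concern.** When parents attend the same session, hear the same peer and discuss with one another, their later self-efficacy scores may be more alike than those of parents from different sessions. This would arise in one arm only, a partially nested design. Such correlation develops after baseline, so baseline covariates cannot be relied on to remove it.

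If it is present and the analysis counts every intervention parent as a separate piece of information, the confidence interval for the program effect is too narrow and the nominal 0.05 test is anti-conservative. Power is also affected: a design set at 80% with independent parents has no reserve for a design effect.

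**Working it through.** **Inputs from the article.** Two-sided α = 0.05, 80% power, 15% dropout, 40 parents per arm and SD 0.76 (Sample size); intervention recruitment from April to October 2023, about 7 months, and stays of 7 to 14 days (Study setting and population).

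**Inputs that must be assumed.** Session-group size m, taken as 2 to 10, and within-group ICC, taken as 0.05 to 0.10. Equal variances in the two arms and equal group sizes are also assumed.

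**1. The plan's own figure.** The formula needs a difference δ, and none is stated, so 80 cannot be reproduced from the article's inputs. Back-solving from the evaluable number, 40 × 0.85 = 34 per arm:

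δ = (1.960 + 0.842) × 0.76 × √(2/34) = 0.516, or 0.68 SD.

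Check with δ = 0.52: n = 2 × 2.802² × 0.76² / 0.52² = 33.5, rounded up to 34; 34/0.85 = 40 per arm. So 80 is consistent with an individual-level calculation without a design effect.

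**2. Clustering in the intervention arm only.**

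- Design effect in that arm: DE = 1 + (m − 1) × ICC
- True SE / naive SE: R = √((1 + DE)/2)
- Shortfall of the naive SE: 1 − 1/R
- Actual type I error of a nominal 0.05 test: 2 × (1 − Φ(1.960/R))
- Power at 34 evaluable per arm, using the correct SE: Φ(2.802/R − 1.960)
- Recruits per arm for 80% power: 17 × (1 + DE), rounded up, then divided by 0.85 and rounded up, where 17 = (2.802/0.679)²

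Example, m = 5 and ICC = 0.10: DE = 1.40; R = √1.20 = 1.095; shortfall 8.7%; type I error 2 × (1 − Φ(1.790)) = 0.074; power Φ(0.598) = 72.5%; 17 × 2.40 = 40.8, so 41 evaluable and 49 recruited.

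| m | ICC | DE | R | Naive SE too small by | Type I error | Power | Recruits per arm |
|---|---|---|---|---|---|---|---|
| 2 | 0.05 | 1.05 | 1.012 | 1.2% | 0.053 | 79.0% | 42 |
| 3 | 0.05 | 1.10 | 1.025 | 2.4% | 0.056 | 78.1% | 43 |
| 5 | 0.05 | 1.20 | 1.049 | 4.7% | 0.062 | 76.2% | 45 |
| 5 | 0.10 | 1.40 | 1.095 | 8.7% | 0.074 | 72.5% | 49 |
| 10 | 0.10 | 1.90 | 1.204 | 16.9% | 0.104 | 64.3% | 59 |

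With ICC = 0 nothing changes. These are large-sample figures; they do not allow for a small number of groups.

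**3. Which rows are plausible.** 40 parents over 7 months is about 5.7 per month. With stays of 7 to 14 days, about 5.7 × 7/30 = 1.3 to 5.7 × 14/30 = 2.7 intervention parents would be in hospital together on average. That points to the first two rows for the session before discharge. The online sessions could pool more parents, but the article does not say whether they did.

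**The case against.** The strongest reply is that the article does not establish the harm. It gives no group size, number of groups or ICC. Statistical methods names neither the subject unit nor the working correlation of the GEE, details that a condensed article may leave to the full plan. This stands: it cannot be said that the analysis certainly treats intervention parents as independent. Only the sample-size formula implies independence.

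A reader might infer that the standard errors are definitely too small. The documents do not support that. It requires shared sessions and a positive residual correlation. If every group received similar content, the program could shift the arm mean without making members of a group more alike.

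A reader might also infer that staff differed between session groups, or that peer sharing and video were given to some groups and not to others. No text says that staff differed by group; Study design refers to the same nurse educators. The optional wording about peer sharing and video in the Intervention group section does not show that delivery varied, and Table 2 lists both as program content. That controls are handled purely individually is likewise an inference, since they share a chat group, although its described use is logistical.

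Finally, the arms are sequential cohorts, so arm is confounded with calendar time. The Limitations section acknowledges susceptibility to secular trends, and modelling session groups does not remove it.

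What remains is that peer sessions are described for one arm only, learning from peers is an intended mechanism, and the printed sample-size formula makes no allowance for resulting correlation. The reply limits the size of the concern; it does not change its direction if the correlation is positive.

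**Conclusion.** The point holds in conditional form. Any positive session-group correlation would make an unadjusted standard error too small and the 0.05 test anti-conservative. The naive SE would be about 1–2% too small for groups of 2–3 with ICC 0.05, which is minor; 5–9% for groups of 5 with ICC 0.05–0.10; and 17% for groups of 10 with ICC 0.10. The first range fits the in-hospital session best, and the last would pool nearly two months of recruitment. All of this rests on assumed group sizes and ICCs, equal variances and large-sample formulas. It is a worthwhile, cheap improvement to the plan, not a demonstrated error.

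**What to change.** - State the size and number of the session groups. Record, or recover from session records, the group that each intervention parent attended; if membership changed between sessions, use the main or first group.
- Analyse the primary outcome with session group as the top-level cluster in the intervention arm, each control parent as a cluster of one, and repeated measures nested within. Use a robust variance with small-sample correction, or a partially nested mixed model.
- If groups are few or membership is unstable, report this as a sensitivity analysis beside the planned GEE, because a cluster-robust variance is itself unreliable with few clusters.
- State in the Sample size section that the 80% power assumes no session-group correlation.

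The cost is one extra variable, a changed model specification and slightly wider confidence intervals. Two practical limits apply. The study period given is October 2022 to May 2024, so membership can be recovered only if session records were kept. Whether the named software, SPSS 26.0, offers the small-sample correction should also be checked before that option is specified.

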## Methods

### Study design

This study protocol outlines a single-center, pre-test, post-test, double-arm quasi-experimental trial with a 1:1 ratio. Randomized controlled trial was deemed infeasible in this setting because concurrent enrollment to parallel arms would likely result in contamination in shared ward and the same nurse educators. The Standard Protocol Items: Recommendations for Interventional Trials can be found in Supplementary File 1. The control group received routine care, and the intervention group received a 1-month self-efficacy promotion program on the basis of usual care. **Table 1** summarizes the program of enrollment, intervention and evaluation. The study has been registered at the Chinese Clinical Trial Registry (23/05/2023, No. ChiCTR2300071721).

**Table 1 T1:** Protocol schedule of enrollment, interventions, and assessments.

Time point	Pre-intervention screening/consent	Allocation	Baseline measurement	PSE promotion intervention	Post-intervention Measurement	Follow-up measurement
	-T1	0	T0	Intervention	T1	T2
Eligibility screen	×					
Informed consent	×					
Allocation		×				
Intervention group			×	×	×	×
Control group			×		×	×
Descriptive characteristics						
Sociodemographic characteristics			×			
ASD-related characteristics			×			
PSOC			×		×	×
PSI-SF			×		×	×
TCS			×		×	×
FQoL			×		×	×
ABC			×			×

ABC, Autism Behavior Checklist; FQoL, Beach Center Family Quality of Life Scale; PSE, Parenting self-efficacy; PSI-SF, Parenting Stress Index-Short Form; PSOC, Parenting Sense of Competence Scale; TCS, Treatment Compliance Scale for Children with Autism Spectrum Disorder.

### Study setting and population

The study is conducted at the child development behavior center of a tertiary hospital in southern China. This center provides ASD diagnosis and structured interventions. Hospitalization is used to provide diagnostic assessment for children with ASD and initiate parent-mediated intervention for children with ASD. The typical hospitalization period is 7 to 14 days. The target population consists of parents of children who have recently been diagnosed with ASD. The study conducted from October 2022 to May 2024. Participants recruited from October 2022 to March 2023 were assigned to the control group, while participants recruited from April to October 2023 were assigned to the intervention group.

### Eligibility criteria

Parents and children who meet the following criteria will be included in the study. For parents, the inclusion criteria are (1) age ≥ 18 years; (2) living with the child; (3) educational level of elementary school or above; (4) proficiency in the use of mobile phones, WeChat, and Tencent meetings and (5) signed informed consent form. The exclusion criteria are (1) diagnosed with severe psychiatric disease, end-stage disease, or any other serious illness, such as cancer; (2) had experienced a serious traumatic event (e.g., car accident, surgery) since the ASD diagnosis; (3) participating in the same type of research; and (4) do not plan to implement the family intervention. For children, the inclusion criteria are (1) diagnosed with ASD by a certified doctor within one year, according to the DSM-5 criteria (32), (2) ASD is the primary diagnosis and (3) age ≤14 years. The exclusion criteria are (1) combined with other intellectual developmental disorders, such as trisomy 21; (2) diagnosed with severe chronic diseases, such as congenital heart disease, and receiving long-term treatment. Only one parent in each family will be included in the study.

